### Blinding

2.6

In order to ensure the consistency of appearance, shape, smell, and specification, Chinese medicine and placebo will be produced, packaged and labeled by the pharmaceutical Department of Affiliated Hospital of Chengdu University of Traditional Chinese Medicine. The statistical professionals unrelated to this study will work out the procedures for designing, distributing, and breaking randomized code lists. The initial parameters about randomized code lists will be sealed in envelopes as confidential data. The emergency letter will be set up in each drug number, including the appropriate drug group. In case of clinical emergency, it can be opened to break randomized code lists. When randomization is broken, researchers, project leaders, and clinical inspectors will be required to participate in the process and record it in detail. Emergency letters will be uniformly recalled after the end of the test. Patients, investigators, and persons performing data analysis will remain blinded from the time of randomization to time of database unlock.

### Diagnostic criteria

2.7

These patients were diagnosed with alcohol dependence according to the criteria of International Classification of Diseases, 10th Edition (ICD-10) and as alcohol use disorders according to the criteria of Diagnostic and Statistical Manual of Mental Disorders, Fifth Edition (DSM-5).

### Eligibility criteria

2.8

Inclusion criteria:

1.Age range 18 to 65 years (both included).2.Diagnosed with alcohol dependence on the basis of the criteria of ICD-10 and DSM-5.3.No obvious withdrawal symptoms and Clinical Institute Withdrawal Assessment for Alcohol (CIWA-Ar) score < 15.4.Michigan Alcoholism Screening Test (MAST) score > 7.5.Informed written consent.

Exclusion criteria:

1.Neuronal degeneration with irreversible process or severe psychiatric disease, for example, a diagnosis of paranoid psychosis, schizophrenia, mental retardation, or bipolar disorder.2.Concomitant drugs therapy against alcohol dependence, such as naltrexone, disulfiram, nalmefene and acamprosate, or other treatment with any of the drugs within 1 month prior to inclusion.3.Concomitant pharmacotherapy with psychotropic medications such as antipsychotics, antiepileptics, mood stabilizers, carbonic anhydrase inhibitors, opioid analgesics, or systemic steroids before enrollment (drug elution periods are allowed, depending on the pharmacokinetic characteristics of the drug).4.Drug Use Disorders Identification Test (DUDIT) score >6 (male), >2 (female), and meeting the substance dependence standards of ICD-10 (except nicotine and caffeine).5.Psychological treatment for mental disorder within the preceding 3 months.6.Having more than 4 unsuccessful hospitalizations for alcohol withdrawal in the past.7.Patients who met the diagnostic criteria of alcohol dependence and had been completely abstinent for more than 2 months.8.Patients who are allergic to ASF.9.Pregnant women, those who plan to become pregnant within 3 months and lactating women.10.Severe physical diseases, including uncontrolled hypertension, cerebrovascular diseases, pulmonary diseases, thyroid diseases, etc (uncontrolled hypertension (systolic blood pressure >180 mm Hg, diastolic blood pressure >110 mm Hg)).11.Those who are preparing for surgery or organ transplantation recently.12.Those who cannot conduct the test as required.13.Severe heart, hepatic and renal dysfunction, or other severely abnormal laboratory tests (cardiac problems defined as decompensated heart failure (New York Heart Association functional class III or IV)), myocardium infarction within the past 12 months and/or unstable angina pectoris; impaired hepatic function (liver transaminases >3 the upper limit of normal); impaired renal function (estimated glomerular filtration rate (eGFR) <60 mL/min); kidney stones; pancreatitis, etc).14.Participants in other drug trials within the last 4 weeks.

### Termination and withdrawal criteria

2.9

Participants will be informed of their right to withdraw at any time. If they withdraw, no further training or questionnaire surveys will be conducted. Before the patients agreed to participate, they are told that if they withdraw, the data collected prior to their withdrawal treatment will be retained and used for analysis, unless they explicitly revoke permission to retain the data. And the reason for withdrawing from the study will be recorded in the case report form. The criteria for termination and withdrawal are as follows:

1.Withdrawing informed consent.2.Treatment failure.3.Adverse events.4.Withdrawing from the study in view of the researcher's consideration of the patient's benefit.5.Unblinding.6.Being likely to commit suicide or violence.7.The combination drugs that have a great impact on the clinical trial, affecting the safety and effectiveness of the therapeutic drugs.8.Being pregnant during treatment.9.Failure to comply with clinical trial medication, that is, the total amount of medication taken by the patient is less than 75% of the planned treatment amount.

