### Outcome measures

3.2

Primary outcomes: The primary outcomes are the changes in the average daily alcohol consumption of the 2 groups before and after treatment and comparison of the scores of the psychological craving self-rating scale during the courses of treatment of 2 groups.

Secondary outcomes: The secondary outcomes include abstinence rates of the 2 groups during the follow-up period, days without consumption, and changes of Short Form Health Survey (SF-36) scores in 2 groups before and after therapy.

The researchers will use weekly self-reports during the follow-up period, clinicians’ judgments, and biochemical examinations to determine whether the patient is abstinent. If the patient has drunk no more than 1 cup since the last visit, the GGT level is normal, or has not increased since the last examination, and the respiratory alcohol concentration is less than 0.10 g/L, the patient is judged to abstain from alcohol.

From the first week to the sixth week, vital signs will be monitored daily. The physical examination will be carried out weekly. The respiratory alcohol concentration will be measured once a week, and drinking craving and adverse events will be evaluated weekly at the time of enrollment and at weeks 2, 4, 6, and 7, serum γ-glutamyl transpeptidase (γ-GT) and blood alcohol concentration will be detected. At weeks 0, 3, and 6, the doctors will give the patients electrocardiograms, and urine pregnancy, blood routine and blood biochemical levels will be detected. During the follow-up period, serum γ-GT and respiratory alcohol concentration will be measured once a week.

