### Compliance

3.5

During the treatment phase, the researchers will record the type, frequency, and dose of any drug received by the patient during the hospitalization, monitor the patient's medication compliance ((drug bags distributed-returned bags)/total number of prescription bags) and other medications taken during the treatment period, and copy any relevant clinical records made at the time of admission. Another researcher who does not participate in the training management and is blinded to the treatment allocation of the patients will contact follow-up interviews including abstinence and TLFB, during the follow-up period after treatment. According to the intention-to-treat principles, patients who withdraw from treatment will still be contacted by researchers for follow-up before completing the 6 weeks of treatment, unless they withdraw from the study.

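### Section 2.9 does not separate stopping study medication from leaving the study, so patients who meet its criteria may have no week-6 or follow-up outcomes

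*Protocol article*

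**What the plan says.** Section 2.9 (Termination and withdrawal criteria) opens with the patient's right to withdraw at any time and gives the consequence: "If they withdraw, no further training or questionnaire surveys will be conducted". It adds that "the data collected prior to their withdrawal treatment will be retained and used for analysis, unless they explicitly revoke permission", and then: "And the reason for withdrawing from the study will be recorded in the case report form". Nine criteria follow under one heading. Withdrawal of consent is the first, followed by "2.Treatment failure.3.Adverse events". Unblinding, interfering drugs and pregnancy come later. The last is poor compliance, defined as "the total amount of medication taken by the patient is less than 75% of the planned treatment amount". Treatment failure is not defined, and adverse events carry no severity threshold.

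Section 3.5 (Compliance) refers to intention-to-treat and says of those who stop treatment early that they "will still be contacted by researchers for follow-up before completing the 6 weeks of treatment, unless they withdraw from the study".

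On outcomes, section 3.2 states: "The primary outcomes are the changes in the average daily alcohol consumption of the 2 groups before and after treatment". The craving score is the other primary outcome, and abstinence during follow-up is a secondary one. Section 3.3 places the TLFB and PACS at week 0, at week 6 and during follow-up. Section 3.8 plans a t test of PACS change from baseline to week 6.

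**The concern.** Stopping the drug and leaving the study are different events. After the first, outcomes can still be measured; after the second, they cannot. Section 2.9 uses one list for both and attaches to withdrawal a rule that ends questionnaires. A site could reasonably apply that rule to every patient who meets any of the nine criteria.

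Several criteria plausibly relate to how the patient is doing (treatment failure) or to the arm (adverse events, tolerability, intake). If assessment ends when they are met, the week-6 comparison and the follow-up abstinence rates rest on a subset selected after randomization. Randomization does not protect that comparison. An analysis plan can choose how to handle missing values, but it cannot recover assessments that were never made.

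**Working it through.** **1. The two sections side by side.** Section 3.5 keeps contact with patients who stop treatment, except those who leave the study. Section 2.9 records reasons for leaving the study and then lists the main reasons why anyone would stop treatment. If all nine criteria count as leaving the study, few treatment stoppers remain for section 3.5 to keep.

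**2. Reach of the 75% rule.** Section 3.1 gives three pouches a day for 6 weeks. Taking the planned amount as the full course (an assumption, since section 2.9 does not say when the rule is judged):
- planned pouches: 3 × 42 = 126
- threshold: 0.75 × 126 = 94.5 pouches
- days of full dosing needed: 94.5 / 3 = 31.5

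A patient who stops for any reason after 31 full days has taken 93 pouches and falls below the threshold. On this reading, anyone who stops in roughly the first three quarters of treatment also meets the compliance criterion.

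**3. What is lost and what is kept.** A patient removed mid-treatment has no week-6 TLFB, no week-6 PACS and no follow-up abstinence assessment. Weekly craving ratings (section 3.2) and weekly alcohol diaries (section 3.3) up to that date are kept.

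**4. Possible size.** The plan gives no figure on this point. The nearest is its 20% dropout allowance (section 2.4: 68 × 1.2 = 81.6, rounded up to 82). Twenty per cent of 82 is 16.4 patients. The withdrawal patterns below are all assumed.

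(a) *Intake in g/day.* Suppose patients who relapse drink 100 and others 10, with relapse proportions r of 0.4 and 0.6. Mean = (1 − r) × 10 + r × 100.
- All assessed: 46 vs 64, difference 18.
- Half of those who relapse unassessed: (0.2 × 100 + 0.6 × 10) / 0.8 = 32.5 and (0.3 × 100 + 0.4 × 10) / 0.7 = 48.6, difference 16.1.
- All of those who relapse unassessed: 10 vs 10, difference 0.

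(b) *True effect 0.5 SD, normal outcome.* Suppose patients above one common intake threshold c go unassessed, 20% overall. Solving for c gives 13.2% of ASF and 26.8% of placebo removed. The observed difference is [0.5 + φ(c + 0.5)/Φ(c + 0.5)] − φ(c)/Φ(c) = 0.30 SD. True differences of 0.3 and 0.8 SD appear as 0.18 and 0.48 SD.

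(c) *No true effect, unequal loss.* Removing the worst share q shifts an arm's mean by φ(z)/(1 − q) SD, where z is the (1 − q) normal quantile. For q = 0.30 the shift is 0.497, and for q = 0.10 it is 0.195. The false difference is 0.30 SD and favours whichever arm loses more. With 41 per arm this is about 12 patients against 4 (0.30 × 41 = 12.3; 0.10 × 41 = 4.1).

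(d) *Abstinence, no true effect.* Take 35.6% in both arms, the midpoint of the two rates in section 2.4. Suppose 30% of non-abstainers are lost in one arm and 10% in the other. Observed rates are 0.356 / (0.356 + 0.644 × 0.7) = 44.1% and 0.356 / (0.356 + 0.644 × 0.9) = 38.1%, a false gap of 6.1 points before rounding.

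**The case against.** The case against is substantial, and much of it stands.

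- **The sentence on questionnaires follows the patient's own right to withdraw.** Applying it to the other criteria is an inference from the shared heading and from the reference to leaving the study. This stands. The text gives no contrary rule, so the ambiguity remains.
- **There is no literal contradiction with intention-to-treat.** A reader might infer one, but the exception at the end of the section 3.5 sentence avoids it and shows that the authors had the distinction in mind. What remains is that section 2.9 does not apply that distinction.
- **Section 3.5 does not clearly end contact at week 6.** A reader might take "patients who withdraw from treatment will still be contacted by researchers for follow-up before completing the 6 weeks of treatment" that way. The mention of 6 weeks more naturally describes when the patient stops, and the preceding sentence speaks of interviews in the follow-up period after treatment.
- **Treatment failure need not mean drinking.** That reading is tempting, but the term is undefined. No link between drinking and adverse events, unblinding or compliance is stated either.
- **The 75% rule does not remove patients from the analysis.** Data gathered before withdrawal are analysed unless permission is revoked. At most, later observations are missing.
- **Part of the craving data is protected.** The mixed linear regression in section 3.8 can use incomplete weekly series. It does not supply the week-6 TLFB or the follow-up abstinence assessment.
- **The illustrations rest on assumptions.** In (a), losing half of the patients who relapse reduces the difference only from 18 to 16.1 g/day, about 11%.

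**Conclusion.** The concern holds in a limited form. Section 2.9 does not separate stopping medication from leaving the study. Read as written, it may end outcome assessment for patients who meet criteria other than withdrawal of consent, and so empty the follow-up that section 3.5 promises under intention-to-treat.

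The documents do not support saying that the worst drinking outcomes are removed, that the two sections flatly contradict each other, or that the bias has a known direction. Loss related to outcome or arm is probable, not certain. Depending on the pattern assumed, the effect runs from slight attenuation to complete loss of a true difference, or to a false difference of about 0.30 SD either way.

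The matter is still worth settling before it affects any patient. The assessments at risk feed both primary outcomes and the abstinence outcome, and they cannot be recovered afterwards.

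**What to change.** Leave the clinical stopping criteria unchanged; which of them should end treatment is not a question for this review. Reconcile sections 2.9 and 3.5 as follows:

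- Define two separate events, stopping study medication and ending follow-up, and record the date and reason for each.
- Continue the scheduled TLFB, PACS and abstinence assessments to week 6 and through the 12-week follow-up for every randomized patient who has not withdrawn consent to follow-up, as far as the patient's condition allows.
- Limit the sentence that ends questionnaires to patients who withdraw that consent.
- Reword section 3.5 so that contact after stopping treatment clearly runs through the 12-week follow-up.
- Analyse all randomized patients in the arm to which they were randomized. Use the 75% intake rule only to define a secondary per-protocol set, not to end outcome assessment.

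The cost is a change of wording and some extra contacts at visits already in the schedule. The sample size does not change.

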## Interventions

3

### Treatment plan

3.1

All patients will receive psychosocial alcohol treatment based on psychological education elements, motivational interviews, and cognitive behavioral therapy, including informing patients about the causes and consequences of alcohol dependence, the necessity of treatment, and how to conduct the treatment of alcohol abstinence. At the same time, family members should be educated about compliance with the treatment plans. Regular psychosocial alcohol treatment was given to abstainers once a week for 6 weeks. According to the abnormal blood chemical features of the patients, the patients will be selectively given corresponding treatment measures such as liver and kidney preservation, correction of electrolyte and acid–base disturbance, effective fluid infusion, vitamin supplementation, etc. The patients with severe withdrawal symptoms during abstinence could be treated with benzodiazepines.

Patients will be randomly assigned to receive ASF or placebo in a ratio of 1:1.

Experimental group (ASF group): On the basis of basic treatment, the patients will take 10 g ASF 3 times daily, dissolved in 150 mL of warm boiling water, for 6 weeks.

ASF used in this test is provided by the pharmaceutical Department of Affiliated Hospital of Chengdu University of Traditional Chinese Medicine (Sichuan, China).

The whole ingredients of ASF are Epimedium 15 g, Semen Ziziphi Spinosae 15 g. One dose every day, 10 g each time, 3 times a day. The herbs in ASF are mixed, processed, filtered, and spray-dried by pressure to form granules, and packaged into single-dose pouches, each weighing 10 g.

Control group: In addition to the basic treatment, the participants will take placebo granules of 10 g each time, 3 times a day. The placebo granules were dissolved in 150 mL of warm boiling water, for 6 weeks.

The placebos in the study are composed of starch and have no active ingredients.

By adding various food pigments, the appearance and taste of the placebo are as close to the real granules as possible.

The drug distribution of the study will be performed by a pharmacist who is not involved in clinical management to preserve the double-blind design. Each time the patient takes the medication, the research nurse will supervise the process and count the number of medication bags taken and not taken.

### Outcome measures

3.2

Primary outcomes: The primary outcomes are the changes in the average daily alcohol consumption of the 2 groups before and after treatment and comparison of the scores of the psychological craving self-rating scale during the courses of treatment of 2 groups.

Secondary outcomes: The secondary outcomes include abstinence rates of the 2 groups during the follow-up period, days without consumption, and changes of Short Form Health Survey (SF-36) scores in 2 groups before and after therapy.

The researchers will use weekly self-reports during the follow-up period, clinicians’ judgments, and biochemical examinations to determine whether the patient is abstinent. If the patient has drunk no more than 1 cup since the last visit, the GGT level is normal, or has not increased since the last examination, and the respiratory alcohol concentration is less than 0.10 g/L, the patient is judged to abstain from alcohol.

From the first week to the sixth week, vital signs will be monitored daily. The physical examination will be carried out weekly. The respiratory alcohol concentration will be measured once a week, and drinking craving and adverse events will be evaluated weekly at the time of enrollment and at weeks 2, 4, 6, and 7, serum γ-glutamyl transpeptidase (γ-GT) and blood alcohol concentration will be detected. At weeks 0, 3, and 6, the doctors will give the patients electrocardiograms, and urine pregnancy, blood routine and blood biochemical levels will be detected. During the follow-up period, serum γ-GT and respiratory alcohol concentration will be measured once a week.

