### Design

2.1

The study is a 6-week randomized, controlled, prospective, double-blind clinical trial. After obtaining informed consent, the 82 alcohol-dependent patients recruited will be randomly divided into the ASF group and the placebo group according to 1:1. The study will include a 6-week treatment period and a 12-week follow up time. Both groups of patients will receive psychosocial alcohol therapy and some conventional symptomatic treatments such as liver protection. Besides, for those with severe abstinence symptoms during abstinence, benzodiazepines can be given as appropriate. On this basis, patients in the ASF group will be treated with 1 dose of ASF 3 times a day, while the control group will receive placebo treatment. The purpose is to evaluate the efficacy and tolerability of ASF in treating patients with alcohol dependence and explore the action mechanism of ASF. The protocol is presented in line with the Standard Protocol Items: Recommendations for Interventional Trials 2013 statement (the SPIRIT figure for the schedule of enrollment, interventions, and assessments is presented in Fig. 1; the checklist of SPIRIT is in Supplemental file 1). The diagram of the study flow is shown in Figure 2.

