### Statistical analysis

3.8

Data analysis will be performed using the SPSS 18.0 statistical software package. Categorical variables will be compared by use of chi-square analysis. Continuous variables between groups will be analyzed by independent sample *T* test. The repeated measure of analysis of variance (ANOVA) will be used to analyze the differences in the group. For all reported values will be expressed as mean ± SEM. The log-rank test will be applied to compare the cumulative probability functions. The Cox proportional hazards model will be applied to assess the hazard ratio of achieving 12 weeks of abstinence and the Kaplan–Meier method will be used to calculate the cumulative probability function of reaching 12 weeks of abstinence. The changes of desire measured by PACS will be compared at baseline and at week 6 through the *T* test. The changes of desire and resistance during the study will be analyzed by using mixed linear regression analysis. All statistical tests will be two-sided tests, and *P* < .05 indicates that the difference is statistically significant.

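### The abstinence rule counts any rise in an above-normal weekly GGT as a failure, so a true abstainer with a stable raised GGT fails about half of the weekly checks by noise alone.

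*Protocol article*

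**What the plan says.** Section 3.2 (Outcome measures) sets three conditions for abstinence, and all must hold:

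- self-report: "If the patient has drunk no more than 1 cup since the last visit";
- GGT: "the GGT level is normal, or has not increased since the last examination";
- breath test: "and the respiratory alcohol concentration is less than 0.10 g/L, the patient is judged to abstain from alcohol".

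The same section says that self-report, clinicians' judgments and biochemistry are all used, but not how a clinician's judgment bears on a GGT rise. On timing it says: "During the follow-up period, serum γ-GT and respiratory alcohol concentration will be measured once a week". Section 2.1 fixes the length: "The study will include a 6-week treatment period and a 12-week follow up time".

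The rule feeds a secondary outcome: "The secondary outcomes include abstinence rates of the 2 groups during the follow-up period". Section 3.8 (Statistical analysis) plans log-rank, Cox and Kaplan–Meier analyses, the last for the "cumulative probability function of reaching 12 weeks of abstinence".

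Section 2.8 sets no GGT limit for entry. Its liver criterion excludes "liver transaminases >3 the upper limit of normal", so patients with raised GGT can be enrolled.

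**The concern.** The GGT condition has two halves. A normal value passes. An above-normal value passes only if it is no higher than at the previous test, which in follow-up was a week before. The threshold for a rise is therefore zero. Two readings of an unchanged quantity differ by assay and biological noise, and the later one is the higher about as often as the lower. A patient who has not drunk, says so and has a clean breath test can then miss the rule on GGT alone.

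Such an error follows liver status rather than drinking. If it is equally common among abstainers in both arms, it scales both abstinence rates down, shrinks their difference and costs power. It would reach the abstinence rate in follow-up, and also the 12-week abstinence analyses if they use the same rule.

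**Working it through.** **1. The plan's own figure.** Section 2.4 gives 54.5% vs 16.7%, alpha 5%, power 90% and 34 per group; section 3.8 makes tests two-sided. The pooled normal formula, with mean rate 0.356 and difference 0.378, gives

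n = [1.960·√(2·0.356·0.644) + 1.282·√(0.545·0.455 + 0.167·0.833)]² / 0.378² = (1.327 + 0.797)² / 0.1429 ≈ 31.6, so 32 per arm.

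The continuity-corrected version gives 37, and the stated 34 lies between. The point does not rest on this figure; 34 per arm is used only in step 5.

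**2. Stable GGT above normal (no outside figure needed).** With independent continuous noise, P(next reading > last) = 1/2 for any CV above zero. Twelve weekly comparisons involve 13 readings. No rise at all requires those readings to fall in strictly descending order, which has probability 1/13! ≈ 1.6 × 10⁻¹⁰. At least one false failure is thus practically certain. Rounding to whole units produces some ties: with an assumed upper limit of 50 U/L, a level of twice normal and CV 5–15%, the weekly rate is 47–49% and the 12-week result is unchanged.

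**3. GGT falling by a constant fraction f per week (f and CV assumed).** P(rise) = Φ( ln(1−f) / (s√2) ), with s = √ln(1+CV²). For example, f = 5% and CV = 10% give s = 0.0998, and Φ(−0.0513/0.1411) = Φ(−0.364) = 36%. The 12-week figures come from simulation and assume that GGT stays above normal throughout, so they are upper figures for patients who normalise.

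| Weekly fall | One comparison (CV 5 / 10 / 15%) | At least one in 12 (CV 5 / 10 / 15%) |
|---|---|---|
| 5% | 23 / 36 / 40% | 99 / 100 / 100% |
| 10% | 7 / 23 / 31% | 60 / 98 / 100% |
| 20% | 0.1 / 6 / 14% | 1 / 53 / 89% |

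**4. GGT falling into the normal range.** Assume decay from 2 times normal towards 0.5 times normal, with half-life 2–4 weeks and CV 5–15%. The result depends on when the fall starts:

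- At the first follow-up reading: 0.6% to 97% of abstainers fail at least once.
- At enrolment, with abstinence through the 6 treatment weeks: GGT enters follow-up at 0.69, 0.88 and 1.03 times normal for half-lives of 2, 3 and 4 weeks. At least one failure then occurs in 0–8% (2–3 weeks) and 6–46% (4 weeks).
- Starting levels of 3–5 times normal at enrolment: 0–98%.

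**5. Power, illustration only.** Suppose a share q of true abstainers is wrongly failed in both arms. The rates become 54.5%·(1−q) and 16.7%·(1−q). Exact power of the two-sided pooled chi-square test at 34 per arm:

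| q | Rates | Power |
|---|---|---|
| 0 | 54.5% vs 16.7% | 93% |
| 20% | 43.6% vs 13.4% | 82% |

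The normal approximation gives 92% and 80%. Nothing in the article gives q.

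**The case against.** The best defence is that the affected group is limited and its size unknown. The 50% result applies only to true abstainers whose GGT stays above normal and does not fall. Normal values are fully protected, and a steep fall with small noise rarely produces a false rise. Six weeks of treatment come before follow-up, so many abstainers may have normalised by then. The lack of a GGT entry limit shows that patients with raised GGT can enter, not that their GGT stays flat. All of this stands, and it rules out any statement of how many patients would be misclassified.

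Three stronger readings are tempting, and the documents do not support them:

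- *That one false rise destroys the 12-week endpoint.* Section 3.8 does not say that 12 weeks of abstinence means an unbroken run of weekly GGT passes. Section 3.3 says that Timeline Follow Back data serve the primary and secondary outcomes, so another derivation is possible.
- *That the trial loses its planned power.* Both primary outcomes (daily consumption and craving) do not use the rule. The planning rates are called withdrawal rates and come from a cited study; that they describe the same outcome is inference.
- *That every patient who misses the rule is recorded as a drinker.* The sentence says who is judged abstinent and does not expressly classify the rest.

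It can also be said that clinicians' judgments may override an isolated rise, and that such detail belongs in a fuller document. This part does not stand. The article states an operative rule with an explicit zero threshold, and an undefined override would make that rule discretionary without repairing it.

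**Conclusion.** The point holds as a defect in a stated outcome definition. For true abstainers with a stable above-normal GGT, the rule gives a false failure at about 50% of weekly comparisons and almost certainly at least one in 12 weeks. This rests only on the noise being independent from week to week and not zero. For falling GGT the 12-week figure lies anywhere from about 0% to 97%, depending on starting level, rate of fall and CV, all of them assumed here.

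The number of patients affected and the resulting power loss cannot be derived from the article. The drop from 93% to 82% shows only what a 20% error in both arms would do to a comparison of 54.5% with 16.7%. The outcome at risk is secondary. The change is worth making because the flaw is certain in kind and cheap to remove, not because its total effect is known to be large.

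**What to change.** Amend the GGT condition in section 3.2. GGT should count against abstinence only if it

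1. is above normal,
2. exceeds the patient's lowest earlier follow-up value by a margin set in advance from the laboratory's own week-to-week variability, and
3. is still above that margin at the next scheduled weekly sample.

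The rule should also name the reference value for the first follow-up test (a week 6 value is already scheduled) and say how a rise first seen at the last test, which has no later sample, is handled. Abstinence on self-report plus breath alcohol, without GGT, should be reported as a sensitivity analysis.

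The lowest earlier value is the better reference because a week-on-week margin misses gradual relapse. Take a 50% margin with confirmation (the 50% is illustrative), CV 10%, and GGT climbing from 1.2 times normal for four weeks and then staying there. A comparison with last week's value detects 15% of relapses at a 20% weekly climb and 47% at 30%. A comparison with the lowest value detects essentially all of them. In stable-GGT abstainers the latter falsely fails 0% to 17% over 12 weeks (CV 5–15%), against practically 100% under the present rule.

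The cost is a revised sentence or two and no new samples. Small undeclared drinking that raises GGT by less than the margin is missed by this condition, and classification waits one week for confirmation.
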